### Sample size

The sample size of 616 patients is determined with a power analysis based on a power of 90%, a significance level of 5%, AL percentage of 4% in the C-seal group and 10% AL in the control group.

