### Statistical analysis

Primary and secondary endpoints will be analyzed on an intention to treat basis. The groups will be compared by means of a Fisher’s exact test.

After 50% and 75% of patient enrollment an interim analysis will be performed based on Snapinn’s stopping rule [12].

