## Discussion

This study investigates the efficacy of the C-seal in the prevention of clinical AL in stapled colorectal anastomoses. The concept of the protection of a colorectal anastomosis by means of an intraluminal device has already been described [13-15]. Based on the idea that intraluminal devices in colorectal anastomoses protect the fecal stream from anastomotic contact, there will be no leakage if anastomotic dehiscence develops. Under the device a perforation can still arise, but because there is no fecal spill this probably will not lead to a fecal peritonitis. Local inflammation may cause adhesions and cover the defect and symptoms of a possible leak are probably less severe [13,16].

It is also hypothesized that AL in colorectal anastomoses is frequently caused by poor vascularization through intraoperative mechanical manipulation [17,18], often from the distal rectal stump [19]. Since the C-seal is attached to the proximal bowel loop, the C-seal remains in situ if the rectal stump is poorly vascularized and leads the fecal stream in the first postoperative weeks outside the body without contact with the rectal wall. After about two weeks the biodegradable drain degrades and is excreted through the anus.

In this study the required sample size is determined based on the current AL rate in the Netherlands. To give a good reflection of the colorectal surgery in the Netherlands and in order to approach this AL incidence, 35 different hospitals, ranging from small referral hospitals to academic centers, are participating in the trial. The participation of this large number of clinics creates possible challenges in protocol adherence. To standardize procedures all operating surgeons are trained by the C-seal research team from the UMCG and during the surgery a student from the C-seal team attends the procedure. To overcome a possible bias regarding the participation of many clinics the randomization is stratified for center.

In addition to the stratification for center, there is also stratified for the intention to create a deviating ostomy and for anastomotic height. The stratification for the intention to create a deviating ostomy is performed to prevent selection bias. The outcome of randomization (C-seal or not) may influence operating surgeons in their decision to create a deviating ostomy. Therefore, the intention to create a deviating ostomy must be documented before the patient is randomized at the OR.

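### The stated 90% power for 616 patients is not delivered by the planned Fisher's exact test: about 80% if two-sided at 5%, about 88% if one-sided at 5%, and sidedness is not stated

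*Protocol article*

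**What the plan says.** The Sample size section of the protocol article is a single sentence. It opens "The sample size of 616 patients is determined with a power analysis" and gives the inputs as a "power of 90%, a significance level of 5%, AL percentage of 4% in the C-seal group and 10% AL" in the control group. The Design section fixes equal allocation, so there are 308 patients per arm.

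The Statistical analysis section names the test: "The groups will be compared by means of a Fisher’s exact test". It then adds two looks at the data: "After 50% and 75% of patient enrollment an interim analysis will be performed", under Snapinn's stopping rule.

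Neither section says whether the 5% level or the Fisher test is one-sided or two-sided. The sample size sentence mentions no allowance for the exact test or for the interim analyses.

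**The concern.** The article publishes the sample size, the power, the level, both event rates and the test, so the five can be checked against each other. An unqualified 5% level is ordinarily read as two-sided, and on that reading 616 is too few for 90% power by any usual formula. The number fits a one-sided calculation with a normal approximation, which is not the test named for the analysis.

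Two things are at stake. If the test is two-sided, the chance of missing the postulated fall from 10% to 4% is about 20% rather than the implied 10%, and a null result would be read with more confidence than the design supports. If the test is one-sided, the power is close to the claim. However, a significant result would then meet only a two-sided 10% standard of evidence, and a reader of the article would not know it.

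**Working it through.** **Inputs.** Control rate p1 = 0.10, C-seal rate p2 = 0.04, level 0.05, power 0.90 (Sample size); 1:1 allocation (Design); Fisher's exact test (Statistical analysis). Sidedness is not given, so both versions are run. No dropout or interim allowance is stated, so none is applied.

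**Step 1: reproduce 616.** The pooled two-proportion formula without continuity correction is

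n per arm = [z_a × √(2 × p̄ × (1 − p̄)) + z_b × √(p1(1 − p1) + p2(1 − p2))]² / (p1 − p2)²

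with p̄ = 0.07, so that:

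- √(2 × 0.07 × 0.93) = √0.1302 = 0.3608
- √(0.0900 + 0.0384) = √0.1284 = 0.3583
- (p1 − p2)² = 0.0036
- z_b = 1.2816

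One-sided 5% (z_a = 1.6449): (0.5935 + 0.4592)² / 0.0036 = 307.8, rounded up to 308 per arm, **616 in total**. This matches exactly.

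Two-sided 5% (z_a = 1.9600): (0.7072 + 0.4592)² / 0.0036 = 377.9, rounded up to 378 per arm, **756 in total**.

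**Step 2: could another formula give 616?** Totals for 90% power at 10% versus 4%:

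| Formula | One-sided 5% | Two-sided 5% |
|---|---|---|
| Pooled, uncorrected | 616 | 756 |
| Pooled, continuity-corrected | 682 | 822 |
| Unpooled | 612 | 750 |
| Simple pooled | 620 | 762 |
| Arcsine | 592 | 726 |

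Only the one-sided uncorrected pooled formula gives 616. No two-sided variant comes near it. The match is to a fixed-sample calculation, so nothing in the number is left over for interim looks or for the conservatism of an exact test.

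**Step 3: power of the test actually planned.** Take two independent binomials with n = 308 each and rates 0.10 and 0.04. For every pair of event counts, compute the Fisher p-value from the hypergeometric distribution. Then add the joint binomial probabilities of all pairs with a p-value at or below the level.

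| Test at 308 per arm | Power | Chance of missing the effect |
|---|---|---|
| Fisher, two-sided 5% | 80.5% | 19.5% |
| Fisher, one-sided 2.5% (check on the row above) | 80.5% | 19.5% |
| Fisher, one-sided 5% | 88.2% | 11.8% |
| Uncorrected normal approximation, one-sided 5% | 90.0% | 10.0% |
| Uncorrected normal approximation, two-sided 5% | 83.3% | 16.7% |

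The stated 90% is met by the one-sided normal approximation and by neither version of Fisher's exact test.

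**Step 4: size at which Fisher's test would reach 90%.** By the same enumeration, 654 patients in total for one-sided 5% and 788 for two-sided 5%. These measure the gap and are not a proposal to enlarge the trial.

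**Step 5: interim looks.** The article names the rule but gives no boundaries, so its effect on power cannot be computed. All figures above are for a single final analysis.

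**The case against.** The strongest defence is that a one-sided test was intended. The objective is directional (a reduction in leakage), and the stated inputs then reproduce 616 to the patient. The full protocol or analysis plan, which is not shown, may state the sidedness. On that reading 616 is no slip, and the gap is under 2 points (88.2% against 90%), from the common practice of sizing with a normal approximation and analysing with an exact test. This stands as far as it goes: the article does not show a miscalculated sample size. It does not rescue the 90%, because no choice of sidedness in an unseen document makes Fisher's exact test reach 90% at 308 per arm with these rates.

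A reader might infer three stronger points that the document does not support:

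- **That the trial simply has 80% power, or that the miss rate is double the claim.** This holds only if the test is two-sided, which the article never says.
- **That the interim analyses take a known further amount of power.** Any figure would need a boundary borrowed from another design.
- **That the planning rate is wrong.** The Discussion says "the required sample size is determined based on the current AL rate in the Netherlands", the Background gives that rate as 11%, and the calculation uses 10%. A size based on a rate need not equal it. With 4% held fixed, 10% is also the more demanding choice: the same formula at 11% versus 4% gives 592 two-sided or 482 one-sided, so 11% does not explain 616 either. This is at most a wording matter.

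**Conclusion.** The concern holds in this form: the quoted power is wrong for the named test on either reading, and the reading itself is left open. The overstatement is about 9.5 points (90% against 80.5%) if the test is two-sided at 5%, and 1.8 points (90% against 88.2%) if it is one-sided at 5%. The larger figure depends on the conventional but unstated two-sided reading.

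These results assume the article's rates of 10% and 4%, 308 analysed patients per arm, an unstratified Fisher's exact test, and one final analysis with no interim cost. That 616 came from a one-sided calculation is an inference from the exact match, not something the article reports.

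**What to change.** Keep 616 patients. Before any interim data are seen:

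1. State in both the Sample size and the Statistical analysis sections whether the primary test is one-sided or two-sided.
2. Replace the 90% with the power Fisher's exact test has at 308 per arm: about 80% for two-sided 5%, the conventional choice, or about 88% for one-sided 5%. If one-sided, add that this corresponds to a two-sided 10% standard of evidence.
3. Note that the quoted power makes no allowance for the two interim analyses.

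The change is to wording only. It adds no patients and leaves the conduct of the trial as it is. The cost is a less favourable quoted power, most visibly if the test is declared two-sided.

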## Abstract

**Background:**

Anastomotic leakage is a major complication in colorectal surgery and with an incidence of 11% the most common cause of morbidity and mortality. In order to reduce the incidence of anastomotic leakage the C-seal is developed. This intraluminal biodegradable drain is stapled to the anastomosis with a circular stapler and prevents extravasation of intracolonic content in case of an anastomotic dehiscence.

The aim of this study is to evaluate the efficacy of the C-seal in reducing anastomotic leakage in stapled colorectal anastomoses, as assessed by anastomotic leakage leading to invasive treatment within 30 days postoperative.

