## Background

Anastomotic Leakage (AL) is the most important complication after colorectal surgery and leads to high rates of morbidity, prolonged hospitalization, commonly requires re-interventions, and can result in death [1].

The incidence of AL varies in the literature between 4 and 20% [2-6]. This considerable variation may be due to the fact that different definitions are used. The International Study Group of Rectal Cancer (ISGRC) proposed a standardized definition for AL according to clinical grading [7]. AL is defined as a defect of the intestinal wall at the anastomotic site leading to a communication between the intra and extraluminal compartments. An abscess in the proximity of the anastomosis is considered to be AL. The severity of AL is classified in three grades. Grade A AL corresponds to the definition ‘radiologic leakage’ for which no intervention is required. Grade B AL requires an active therapeutic intervention but could be managed without relaparotomy. Grade C AL requires a relaparotomy [7].

Recent data from the Dutch Surgical Colorectal Audit (DSCA) showed an AL rate of 11% leading to re-intervention in the Netherlands [8].

In order to reduce the incidence of AL the C-seal is developed. The C-seal is an intraluminal biodegradable drain which is stapled to the anastomosis with a circular stapler [9]. The C-seal covers the intraluminal side of the anastomosis and prevents extravasation of intracolonic content to the peritoneal cavity in case of anastomotic dehiscence.

In previous studies performed in the University Medical Center Groningen (UMCG) and in some other clinics a total amount of 52 patients were treated with the C-seal. The pilot study of fifteen patients, who underwent a colorectal resection with a C-seal, showed that the application of the C-seal was feasible and there were no clinical or radiological signs of leakage [10]. Also the subsequent phase II study with 37 patients confirmed the feasibility of the C-seal by both surgeons and by patients. There were no serious adverse events reported related to the C-seal [11]. Furthermore this study showed promising results in the reduction of clinical AL, which led to the initiation of a randomized controlled trial, the C-seal trial. This trial aims to compare the outcome for stapled colorectal anastomoses made with and without a C-seal.

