## Methods

### Design

The C-seal trial is a prospective multi-center randomized controlled trial, initiated by the department of surgery, division of abdominal surgery of the UMCG, the Netherlands. The study will be performed in approximately 35 clinics.

In this trial 616 patients will be randomized equally between the C-seal group and the control group. The study protocol is approved by the central medical ethics committee of the UMCG. In all participating centers a local feasibility agreement is arranged. Patients will be followed until one year after randomization.

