### Intervention

Fifty percent of the study population will be randomized to the C-seal group and 50% to the control group. The C-seal is stapled to the anastomosis with a circular stapler. Before creating the anastomosis the C-seal is attached to the anvil of the circular stapler (Figure 1) and together they are inserted in the proximal bowel loop. After firing the circular stapler the C-seal is stapled to the mucosal side of the afferent loop (Figure 2). When the stapler is removed from the anus, the C-seal is brought through the anus and cut from the stapler anvil. The application of the C-seal to the anvil is trained in a practicum session provided to the participating operating surgeons and local research group.

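### The 10% control rate departs without explanation from the 11% national rate it is said to rest on, and at 10% vs 4% the planned Fisher's exact test falls short of the stated 90% power

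*Protocol article*

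**What the plan says.** The Sample size section of the protocol article derives 616 patients from 90% power, a 5% significance level and an "AL percentage of 4% in the C-seal group and 10% AL in the control group". It does not say whether the 5% is one- or two-sided. The Design section splits the patients evenly: "In this trial 616 patients will be randomized equally between the C-seal group and the control group".

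The Discussion gives the origin of the calculation: "In this study the required sample size is determined based on the current AL rate in the Netherlands". The document states one such rate. The Background reports that recent national audit data "showed an AL rate of 11% leading to re-intervention in the Netherlands", and the abstract repeats the figure ("with an incidence of 11% the most common cause of morbidity and mortality"). The Background figure is for leakage that led to re-intervention, which is the trial's primary event.

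The Statistical analysis section names Fisher's exact test for the comparison, without sidedness, and plans interim analyses after 50% and 75% of enrolment.

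**The concern.** One calculation carries two control rates. The Discussion points to the national rate, the Background puts it at 11% for the same event as the primary endpoint, and the calculation uses 10%. A different event definition therefore does not explain the gap, and the text does not describe the 10% as rounded or as deliberately cautious.

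With event rates this low, small changes in the inputs move power a good deal. That raises two questions: which rate produced 616, and whether 616 patients give the named test the stated 90% at that rate. If they do not, readers and those who judge the interim results are relying on a power that the planned analysis does not have.

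**Working it through.** **Inputs.** 616 patients, 1:1, so 308 per arm (Design; Intervention). Power 90%, significance level 5%, rates 4% and 10% (Sample size). National rate 11% (Background). Fisher's exact test (Statistical analysis). Sidedness is not stated, so both readings are shown. The interim looks are left out.

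**Step 1: reproduce 616.** The pooled-variance formula without continuity correction is

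n per arm = [z(α)·√(2·p̄·(1−p̄)) + z(power)·√(p1(1−p1) + p2(1−p2))]² / (p1−p2)²

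For 4% vs 10%: p̄ = 0.07, √(2 × 0.07 × 0.93) = √0.1302 = 0.3608, and √(0.0384 + 0.0900) = √0.1284 = 0.3583. With z(power) = 1.2816:

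- One-sided 5%: (1.6449 × 0.3608 + 1.2816 × 0.3583)² / 0.0036 = 307.8, so 308 per arm and **616** in total.
- Two-sided 5%: (1.9600 × 0.3608 + 1.2816 × 0.3583)² / 0.0036 = 377.9, so 378 per arm and 756 in total.

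**Step 2: see whether 11% vs 4% could be the source.** The same formula at 90% power gives 592 in total two-sided (295.4 per arm) and 482 one-sided (240.6 per arm). With continuity correction the totals are 648 and 538. None is 616. The stated 10% gives an exact match and 11% does not, so 10% is evidently the rate used.

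**Step 3: power of the named test.** For every pair of event counts in two arms of 308, compute Fisher's p-value and add up the binomial probabilities of the pairs with p ≤ 0.05. The two-sided p-value sums all tables no more probable than the one observed; the one-sided p-value takes the tail favouring C-seal.

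| Control vs C-seal | Fisher, two-sided 5% | Fisher, one-sided 5% |
|---|---|---|
| 10% vs 4% (as stated) | 80.5% | 88.2% |
| 11% vs 4% | 89.9% | 94.5% |

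**Step 4: where the shortfall at 10% vs 4% comes from.** The one-sided pooled formula gives 90.0% at 308 per arm. Using Fisher's test instead, still one-sided, gives 88.2%, a loss of 90.0 − 88.2 = 1.8 points. Making it two-sided gives 80.5%, a further loss of 88.2 − 80.5 = 7.7 points. The control rate is 10% throughout, so it contributes nothing to this loss.

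**Step 5: is 10% the cautious choice?** At 11%, two-sided Fisher power is 89.9% with C-seal held at 4%, 84.8% with the relative risk held at 0.4 (4.4%), and 75.2% with the six-point difference held (5%). Against 80.5% at the stated rates, 10% is the cautious input in the first two cases but not in the third. The stated inputs fix the C-seal rate at 4%, which is the first case.

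**The case against.** The best defence is that a size based on a national rate need not use it to the digit. Planning at 10% when the audit shows 11% fits rounding or modest caution. With C-seal at 4% the lower control rate asks for more patients, so the trial gains power if the true control rate is 11%. This stands, and it makes the one-point gap a matter of wording. It does not remove the conflict with the Discussion, because nothing in the article gives that reason.

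It can also be said that 616 is arithmetically correct for the stated rates. That stands too, but only for a one-sided normal-approximation test. The article plans Fisher's test, and with that test the stated 90% is not reached on either reading.

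Two stronger readings are tempting. A reader might infer that the design alternative is unknown. It is not: the Sample size section states it, and 616 follows from it exactly. A reader might also infer that 11% vs 4% was the real basis, since two-sided Fisher power is then 89.9%. That is a near match only. The two-sided Fisher test first reaches 90% at 310 per arm (620), and no standard formula checked gives 616 at those rates.

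Finally, sidedness may be settled in a full protocol or analysis plan that is not shown, so its absence from the article is not in itself counted as an error. The shortfall does not depend on how it is settled; only its size does.

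**Conclusion.** The point holds in two parts of unequal weight. First, the stated basis (11%) and the input used (10%) differ without explanation; this is minor. Second, at the stated 10% vs 4% with 308 per arm, the named test has 80.5% power if two-sided at 5% and 88.2% if one-sided, not 90%. The shortfall is about 9.5 points on the usual two-sided reading and about 1.8 points on the one-sided reading.

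A reader might blame the control rate, since moving it from 10% to 11% shifts two-sided power by 89.9 − 80.5 = 9.4 points. The documents do not support that. The calculation evidently used 10%, and most of the loss at that rate comes from pairing a one-sided sample size with a two-sided test.

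The figures assume equal arms of 308, complete primary outcome data and no adjustment for the interim analyses. The 11% vs 4% figures also assume that the C-seal rate stays at 4%.

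**What to change.** - **Sample size:** keep 10% vs 4%, state whether the 5% is one- or two-sided, and restate the power for Fisher's exact test with 308 per arm, before interim looks: about 80% if two-sided, about 88% if one-sided.
- **Discussion:** say that a control rate of 10% was assumed against a cited national rate of 11%, and why. Power at 11% vs 4% (89.9% two-sided, 94.5% one-sided) may be added, labelled as a sensitivity figure.
- **Avoid:** replacing the design alternative with 11% vs 4% to recover 90%. That would be fitted after the fact, would raise the assumed effect from six to seven points, and would hide how 616 was obtained.

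The cost is two sentences and a less favourable stated power. Enrolment stays at 616. For scale, keeping 90% power with a two-sided Fisher test at 10% vs 4% would take about 788 patients (394 per arm); this correction does not ask for that.

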### Randomization

Patients are equally distributed to either the C-seal or the control group. In an attempt to overcome possible bias, the randomization procedure is performed in the operating room during surgery. The randomization procedure is performed by a C-seal student with an online randomization system. The randomization is stratified for center, high or low anastomosis (respectively proximal or distal of the peritoneal reflection) and the intention to create a temporary deviating ostomy.

### Statistical analysis

Primary and secondary endpoints will be analyzed on an intention to treat basis. The groups will be compared by means of a Fisher’s exact test.

After 50% and 75% of patient enrollment an interim analysis will be performed based on Snapinn’s stopping rule [12].

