A limitation of the study may be that we have chosen not to stratify for neoadjuvant therapy. Most patients with rectal cancer in the Netherlands are treated with neoadjuvant radiotherapy. From the literature it is concluded that short scheme radiotherapy is not a significant risk factor for the occurrence of AL [20,21]. Results of studies with long scheme chemo radiation however are inconsistent in the influence on the incidence of AL. Some studies describe a significant increase in the occurrence of AL [22,23], while results from other studies did not found this increase in the incidence of AL [24,25].

Because a large study population will be included in this trial, the patients will be proportionally allocated to both groups.

With the results of this randomized controlled trial we compare the incidence of AL leading to re-intervention in patients treated with a C-seal to patients treated without a C-seal.

Secondary to this prospective trial a few side studies will be performed. With the use of intraoperative collected data of anaesthesiological parameters as oxygenation, blood tension, temperature and the use of vasoconstrictive medication eg, we attempt to identify potential contributing factors for the occurrence of AL. Also intraoperative data of the technical aspects of the stapling process are noted in the CRF to evaluate the surgical technique used to create an anastomosis in the Netherlands and the possible relation this could have in causing AL. Adjacent to the clinical trial translational research will be conducted with blood draws and bowel samples of the proximal and distal donuts of the included patients, collected during the surgery. With these patient materials we aim to correlate molecular tissue characteristics as pro-inflammatory proteins, Matrix Metallo Proteinases and C-reactive protein with clinical outcome. In blood plasma, indicators of inflammation, bacterial translocation and intestinal damage will be determined and will be correlated with the molecular profile of the patients.

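### The primary test is an unstratified Fisher's exact test: conservative at these event rates, it costs about 3 points of power one-sided or 4 to 5 two-sided, and ignores the randomisation strata

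*Protocol article*

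**What the plan says.** The Statistical analysis section of the protocol article names one test: "The groups will be compared by means of a Fisher’s exact test". It mentions no stratum, and it applies the test within an intention-to-treat analysis with interim looks at 50% and 75% of enrolment.

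The Randomization section sets out a stratified design: "The randomization is stratified for center, high or low anastomosis (respectively proximal or distal of the peritoneal reflection". Its third factor is whether the surgeon plans a temporary ostomy. The Discussion adds that ostomy intention must be documented before the patient is randomised.

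The Design section fixes the size: "In this trial 616 patients will be randomized equally between the C-seal group and the control group". The Sample size section says that this was "determined with a power analysis based on a power of 90%, a significance level of 5" per cent, with "AL percentage of 4% in the C-seal group and 10% AL in the control group". It does not say whether the 5% is one-sided or two-sided, or which test the calculation assumed.

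**The concern.** Two features of the chosen test do not suit this trial.

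- **It is conservative.** Fisher's test conditions on the total number of leaks. With about 43 leaks expected, only a few splits between the arms lie near the 5% boundary, so the test usually operates well below its nominal level. The unused type I error is lost power.
- **It pools over the strata.** The trial balances the arms within strata, and the usual practice is to analyse by the factors used to randomise.

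At stake are a few points of power in a trial that states 90%. They can be recovered without recruiting anyone further.

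**Working it through.** **Inputs.** From the article: 616 patients allocated 1:1, hence 308 per arm; leak rates 10% and 4%; significance level 5%; power 90%; about 35 clinics. Assumed, because the article gives none: stratum sizes, stratum odds ratios and centre variation. Interim looks are ignored throughout.

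**1. Reproduce 616.** Pooled z-test without continuity correction, mean rate 0.07:

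n per arm = [z_α·√(2·0.07·0.93) + z_β·√(0.10·0.90 + 0.04·0.96)]² / 0.06²

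- One-sided 5%: [1.6449·0.3608 + 1.2816·0.3583]² / 0.0036 = 1.0527² / 0.0036 = 307.9, so 308 per arm and 616 in total. This matches exactly.
- Two-sided 5%: [1.9600·0.3608 + 1.2816·0.3583]² / 0.0036 = 1.1664² / 0.0036 = 377.9, so 378 per arm and 756 in total. This does not match.

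Both bases are carried forward, because the article states neither.

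**2. Exact power and size at 308 per arm,** by summing over all binomial outcomes:

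| Basis | Test | Power, 10% vs 4% | Size at common rates of 4-12% |
|---|---|---|---|
| Two-sided 5% | Fisher | 80.5% | 3.2-3.7% |
| Two-sided 5% | Pearson | 85.0% | 5.0-5.2% |
| Two-sided 5% | Fisher mid-p | 83.9% | 4.7-4.9% |
| One-sided 5% | Fisher | 88.2% | 3.1-3.9% |
| One-sided 5% | Pearson | 90.9% | 5.0-5.1% |

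The loss from Pearson to Fisher is 4.5 points two-sided (84.97 − 80.47) and 2.8 points one-sided (90.93 − 88.16). Both tests are unstratified, so none of this loss is due to the strata.

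An example: 308 × (0.10 + 0.04) = 43.1 leaks are expected. If 43 occur and split 28 to 15, two-sided Fisher gives p = 0.057 and Pearson p = 0.040. Fisher needs 29 to 14 (p = 0.026).

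In patients: two-sided Fisher reaches 85% power at about 345 per arm, 37 more than planned (345 − 308).

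**3. Add the strata.** 200,000 simulated trials per scenario, four strata (height by ostomy intention) of 108, 46, 62 and 92 patients per arm, and a common treatment odds ratio giving 10% versus 4% overall. Two-sided 5%:

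| Assumed stratum odds ratios | Fisher | Pearson | CMH | CMH − Fisher | CMH − Pearson |
|---|---|---|---|---|---|
| 1, 1, 1, 1 | 80.37% | 84.85% | 84.54% | 4.2 | −0.3 |
| 1, 1.5, 2, 3 | 80.60% | 85.05% | 85.06% | 4.5 | 0.0 |
| 1, 2, 3, 6 | 80.92% | 85.41% | 85.67% | 4.8 | +0.3 |
| 1, 3, 6, 12 | 81.01% | 85.59% | 86.16% | 5.2 | +0.6 |

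One-sided 5%, CMH gives 90.9-92.0% against Fisher's 88.0-88.7%, a gain of 2.8-3.3 points. At common rates of 7% and 10%, size over both bases is 4.9-5.1% for CMH. For Fisher it falls as low as 3.0% when the strata are strongly prognostic.

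**4. Add centre.** A simulation with 35 centres, assumed blocks of 4 and an assumed centre SD of 0.5 gave two-sided power of 82.9% for Fisher, 85.4% for CMH over four strata and 82.2% for CMH over all cells. Sizes were 3.7%, 4.5% and 5.0%. The four-stratum gain is 85.4 − 82.9 = 2.5 points. A second, rougher simulation with the same assumed SD put CMH including centre at 83.7-84.2% against Fisher's 82.5%. Stratifying fully by centre therefore gives anything from a small loss to a gain of 1 to 2 points. The cells are sparse: 35 × 2 × 2 = 140, or 616 / 140 = 4.4 patients and 43.1 / 140 = 0.3 leaks per cell.

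**The case against.** The strongest reply is that Fisher's test is prespecified, familiar and valid. Its type I error stays below the nominal level, so it cannot manufacture a positive result. That stands: the present plan is safe, only less efficient than it could be.

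Other points against the concern also stand, and they limit it:

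- **Cause.** A reader might infer that ignoring the stratification factors is what wastes power. The calculation does not support this. Pearson's unstratified test already recovers the loss, and CMH differs from it by −0.3 to +0.6 points. The article also gives no stratum risks, so it does not establish that the strata are strongly prognostic. Its stated reasons for stratifying by centre and ostomy intention concern bias.
- **Sidedness.** A loss of 4 to 5 points presumes a two-sided test. On the one-sided basis that yields 616 it is about 3 points.
- **Centre.** CMH over four strata ignores centre, as Fisher's test does. With assumed centre variation its gain shrinks to about 2.5 points.
- **Omissions.** A reader might fault the absence of an effect estimate or adjusted model. An article may leave these to the full protocol or analysis plan.
- **Neoadjuvant therapy.** A reader might also fault the Discussion's reliance on trial size for balance ("the patients will be proportionally allocated to both groups"). The article itself discloses the lack of stratification as a limitation and calls the evidence on long-scheme chemoradiation inconsistent. It adds nothing to this point.

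What remains is that the article fixes a specific test, and a better-matched one is available at no cost in patients.

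**Conclusion.** The point holds as an efficiency improvement. The named test runs at a true size of about 3.0-3.9%. It gives up about 3 points of power one-sided and 4 to 5 points two-sided, or about 2.5 points two-sided with assumed centre variation. Almost all of this is Fisher's discreteness; stratification itself moves power by less than 1 point under the assumed stratum risks.

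On the one-sided basis the choice of test decides whether the stated 90% is met: 88.2% with Fisher, 90.9% with Pearson. On the two-sided basis neither test reaches it. A reader might blame Fisher's test for the whole two-sided gap between 80.5% and 90%, but about half of it (90 − 85.0 = 5.0 points) remains with Pearson and is a matter of sample size and sidedness.

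A reader might also infer a validity error. There is none, since type I error is not inflated.

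The Fisher and Pearson figures in the exact table need only the article's rates and numbers plus a choice of sidedness. The CMH and centre figures rest on the assumed strata, odds ratios and centre SD.

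**What to change.** In the Statistical analysis section:

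1. Make the primary test a CMH test stratified by anastomotic height (high or low) and ostomy intention (yes or no), as recorded at randomisation. Report the Mantel-Haenszel risk difference with a 95% CI.
2. State whether the 5% level is one-sided or two-sided, in agreement with the Sample size section.
3. Keep Fisher's exact test as a sensitivity analysis.
4. Handle centre in a sensitivity model, for example logistic regression with a random centre intercept, because about 140 cells are too sparse for full stratification.

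The cost is a few sentences. Both factors are known before allocation, so no new data or patients are needed. Make the change before the interim analysis at 50% of enrolment, so that interim and final analyses use the same test.
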